### **9.4 Interim analysis (if applicable)**

not applicable

## 10 ETHICAL CONSIDERATIONS

### 10.1 Regulation statement

The study will be conducted according to the principles of the Declaration of Helsinki and in accordance with the Medical Research Involving Human Subjects Act (WMO).

### 10.2 Recruitment and consent

Recruitment will take place at the community mental health centre in Maastricht. Subjects will be made aware of the possibility to participate in this study by their supervising care givers. In case subjects show interest they will be invited by the investigator of this study who will provide them with all information about the study and risks, benefits and rights of participants. Subjects have a week to decide whether or not they want to participate. In case a subject does not want to participate, but changes his/her mind later, he or she can still participate.

### 10.3 Objection by minors or incapacitated subjects (if applicable)

Not applicable. Only adults (>18 years) and capacitated individuals will be included in the study.

### 10.4 Benefits and risks assessment, group relatedness

There are no health risks associated with the research.

There is a personal benefit for subjects in that they are offered to receive an extra training that is expected to improve their resilience against depression. There is scientific evidence for the notion that MBCT training has positive effects on mental health and decreases strongly the relapse rate for depression (with around 20-30%, leaving only half of the normal relapse rate) in subjects in remission of depression.

There is a scientific benefit in that it leads to greater insight into the biological and psychological factors related to resilience, which will be important for prevention of depressive disorder in the population.

Burden for the patients is some time investment. After the screening subjects have to come twice for a meeting in which they are interviewed concerning depressive symptoms and fill in some questionnaires (2 x 1 hour). At the baseline meeting subjects have to spit some saliva in a tube. This will take only a minute. They participate twice in the ESM protocol (6-day period of filling in dairies concerning daily life events and mood). This procedure will costs approximately 4,5 hours in total for the two periods. Before the start of each ESM protocol they have to come for a short meeting (15 -30 min) to receive specific instructions related to this procedure.

**10.5 Compensation for injury**

There are no health risks related to this study. Dispensation from the statutory obligation to provide insurance is requested.

**10.6 Incentives (if applicable)**

Subjects will receive free MBCT training. Subjects that are randomized to enter the control group are offered an MBCT course that they can follow later, after the study. In addition, they receive some financial compensation in relation to the amount of time they invested in the study, with a maximum of 50 euro. In addition, subjects are fully compensated for any travel costs related to the study.

## 11 ADMINISTRATIVE ASPECTS AND PUBLICATION

### 11.1 Handling and storage of data and documents

Data are handled confidentially and if possible anonymously. The data are coded using a number indicating the order of entry. Only the main investigator ([name]) has permission to access the source data. Where it is necessary to be able to trace data to an individual subject, a subject identification code list is used to link the data to the subject. The key to the code is safeguarded by the investigator. Collected material is coded and will be stored with the purpose of analysis. After material is analysed it will be destroyed. The handling of personal data complies with the Dutch Personal Data Protection Act (in Dutch: De Wet Bescherming Persoonsgegevens, Wbp).

### 11.2 Amendments

*<The following text is applicable for studies without an investigational medicinal product.>*

Amendments are changes made to the research after a favourable opinion by the accredited METC has been given. All amendments will be notified to the METC that gave a favourable opinion.

All substantial amendments will be notified to the METC and to the competent authority.

Non-substantial amendments will not be notified to the accredited METC and the competent authority, but will be recorded and filed by the sponsor.

### 11.3 Annual progress report

The sponsor/investigator will submit a summary of the progress of the trial to the accredited METC once a year. Information will be provided on the date of inclusion of the first subject, numbers of subjects included and numbers of subjects that have completed the trial, serious adverse events/ serious adverse reactions, other problems, and amendments.

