**Objective:**

- 1) Can the ability to experience reward in daily life be experimentally modified?
- 2) How does experimental modification of reward impact on depressive symptomatology and can individual variation be traced to genetic variation.

**Study design:** An intervention study is used in which subjects are randomized to treatment as usual (TAU) or TAU + mindfulness-based cognitive therapy. Experience Sampling Method (ESM) is a structured diary, momentary assessment technique to study subjects in their daily life. Before and after the intervention subjects undergo a six-day period of ESM assessment. Subjects will be globally informed, but remain blind as to how ESM measures relate to testing the hypothesis.

**Study population:** A sample of 120 depression-remitted adult subjects with residual symptomatology (Ham-17>7) recruited from the community mental health centre in Maastricht (CMHC).

**Intervention (if applicable):** The experimental group receives 8 weeks of mindfulness training by an experienced trainer in addition to their normal treatment, if any. Sessions are weekly (2,5 hours a session) and subjects receive daily homework exercises. The control group continues their normal treatment, if any.

**Main study parameters/endpoints:** The increase in reward experience in daily life, whereby reward experience is conceptualised as the effect of small daily life positive events on positive mood state. Since ESM measurements are performed 10 times a day for 6 days, there will be a maximum of 60 measurements within each subject concerning effects of positive events on positive mood state in the flow of daily life.

**Nature and extent of the burden and risks associated with participation, benefit and group relatedness:** There are no health risks associated with participation. There is a personal benefit for subjects in that they are randomized to receive an extra training that is expected to improve their resilience against depression. Time investment for subjects is 2,5 hours for questionnaires (distributed over three meetings, including the screening). In addition, they participate twice in the ESM protocol (6-day period of filling in dairies concerning daily life events and mood). Before the start each ESM protocol they have to come for a short meeting (15 -30 min) to receive specific instructions related to this

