### 4.2 Inclusion criteria:

We want to include adult subjects with:

1. a previous episode of major depressive disorder according to DSM-IV criteria
2. residual depressive symptoms: score > 7 on Hamilton Depression Rating Scale (HAM-17), for at least two weeks.

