### 7.3 Study procedures

First, subjects are screened for the participation criteria and fill in a questionnaire concerning demographic variables.

At baseline subjects:

- undergo Psychiatric interviews: SCID-I and the Hamilton Depression Rating Scale (HAM-17).
- fill in some questionnaires concerning depressive symptoms (SCL-90), personality (NEO-PI) rumination (RRS), life events (Interview for Recent Life Events) and early adversity (Childhood Trauma Questionnaire)
- spit some saliva in special tubes as to measure polymorphisms/haplotypes in the DNA that have been associated in previous studies with the brain reward system. (Since insights concerning relevant polymorphisms and haplotypes change rapidly, an up-to-date relational (i.e. cross-relating genotype, phenotypic expressions, biochemical pathways) database relevant for the neurosciences is maintained within our department. Genetic analyses thus are always matched against the most recent information).
- participate in the 6-day ESM period as described under 'study design'. Subjects will be briefed and de-briefed before and after the ESM period, respectively.

Subjects randomized to the experimental group will participate in an 8-week-period of MBCT, including weekly sessions of 2,5 hours in which the training takes place and daily homework exercises. They also fill in to what degree they complied with the homework exercises every day (in minutes).

After the intervention, subjects from both groups (experimental and control) again undergo the psychiatric interviews and the questionnaires.

In addition, they participate in another 6-day ESM period and are again briefed and de-briefed with respect to this procedure. The ESM debriefing includes the collection of the diaries and discussion concerning unclarities or missing values.

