### 7.4 Withdrawal of individual subjects

Subjects can leave the study at any time for any reason if they wish to do so without any consequences. The investigator can decide to withdraw a subject from the study for urgent medical reasons.

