## **8 SAFETY REPORTING**

Not applicable

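### Safety reporting is set aside in section 8 but serious adverse events are promised to the ethics committee each year in 11.3, with no procedure to collect them

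*Protocol*

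**What the plan says.** Section 8 (Safety reporting) contains only "Not applicable". Section 11.3 (Annual progress report) lists what goes to the ethics committee once a year, including "numbers of subjects that have completed the trial, serious adverse events/ serious adverse reactions, other problems, and amendments".

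The absence of risk is stated three times. The Summary says "There are no health risks associated with participation". Section 10.4 says "There are no health risks associated with the research". Section 10.5 repeats the point and adds "Dispensation from the statutory obligation to provide insurance is requested".

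Four other places bear on the question:

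- Section 4.2 admits people with a previous major depressive episode and "residual depressive symptoms: score > 7 on Hamilton Depression Rating Scale (HAM-17), for at least two weeks".
- Section 7.3 has subjects at baseline "undergo Psychiatric interviews: SCID-I and the Hamilton Depression Rating Scale (HAM-17"), and repeats the psychiatric interviews and questionnaires in both groups after the intervention.
- Section 7.4 allows for medical withdrawal: "The investigator can decide to withdraw a subject from the study for urgent medical reasons".
- Section 7.6 has people who stop treatment asked for their reason, and compares their characteristics with those of the others.

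**The concern.** One section says that safety reporting does not apply; another promises a yearly account of serious adverse events. A team that follows section 8 has no instruction to gather what 11.3 says it will submit.

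This matters because of who is enrolled. People with earlier major depression and current residual symptoms can have a hospital admission, an episode of self-harm or a recurrence during the study, in either arm and whether or not the training plays any part. The no-risk statement also does some work: section 10.5 sets it beside a request to be released from the insurance obligation. A statement used in that way should rest on events that were looked for.

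**Working it through.** No formula or stated figure is involved, so the check sets the sections against each other.

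**Step 1: is there a contradiction in current text?** Yes. Section 8 declares the topic inapplicable, and 11.3 lists serious adverse events among the contents of the annual report. Section 11.3 is ordinary protocol text, with no template prompt attached.

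**Step 2: does another section supply the procedure?** No. The procedures in 7.3 contain no adverse-event item. Adverse-event terms otherwise appear only in the list of abbreviations, and no section gives a collection window, a responsible person or a form. A statistical analysis plan could say how events are tabulated, but it could not create data that the protocol does not set out to collect.

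**Step 3: what would be captured anyway?**

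| Type of event | Route in the protocol | Captured? |
|---|---|---|
| Depressive worsening or new episode, subject returns | Repeated SCID-I and HAM-17, both arms (7.3) | Yes, by the same instruments in both arms |
| Problem that leads a subject to stop treatment | Reason asked (7.6) | In part; the control arm has no study treatment to stop, so its counterpart is unclear |
| Serious event between assessments, subject continues | None stated | No systematic route |
| Self-harm, admission or other harm that is not a depressive episode | None stated | No systematic route |
| Event in a subject who does not return | At most the reason for stopping (7.6) | No stated assessment after withdrawal |

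The last row includes anyone withdrawn for urgent medical reasons under 7.4. Serious events may well be concentrated in that group.

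**Step 4: can a size be given?** Not for the contradiction itself. As an illustration only of what simple recording would allow: if the 120 subjects were split equally (the protocol gives no ratio), there would be 120/2 = 60 per arm. Zero serious events in 60 would put the one-sided upper 95% limit at about 3/60 = 5% (exactly, 1 − 0.05^(1/60) = 4.9%). With 50 assessed per arm after drop-out, also an assumption, it would be about 3/50 = 6%. The point does not rest on these figures.

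**The case against.** The strongest reply is that the harm that matters most in this population is already measured. The SCID-I and HAM-17 are repeated in both arms, by the same method, in everyone who returns, and reasons for stopping treatment are asked. That stands. A reader might infer from section 8 that harms would go unrecorded, or that the annual report would have nothing behind it. The protocol does not support either reading, because 7.3 and 7.6 supply part of the data and 11.3 is itself a commitment to report.

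A second reply is that the risk statements concern risks arising from the research. Recurrence or admission caused by the underlying illness would not contradict them, and the withdrawal clause in 7.4 is a general provision. This also stands: the protocol does not show the statements to be false. They are an ethical risk assessment, and section 2 contains no safety objective.

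A third tempting inference is that events would be noticed more often in the training arm, which is seen weekly for 8 weeks, while no contact with controls between assessments is described. That is plausible for unsolicited events, but no section says that trainers note or pass on events. It does not apply to the depressive outcomes, which are assessed alike in both arms.

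Finally, 11.3 may be retained template wording, since neighbouring sections still carry template prompts. It is current text all the same, and it conflicts with section 8.

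**Conclusion.** The concern holds in a limited form. Sections 8 and 11.3 contradict each other, and the protocol neither defines serious adverse events nor says how they are collected. Three kinds of event have no systematic collection route: serious events between the two assessments, harms other than depression, and events in subjects who do not return. As a result 11.3 cannot be met reliably, and the no-risk statements in the Summary, 10.4 and 10.5 can be checked only in part.

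The conclusion rests on the protocol alone and assumes that no separate study manual fills the gap. It does not touch the primary endpoint, the sample size or the multilevel analysis. It is a cheap improvement in patient safety and internal consistency.

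**What to change.** 1. Replace the entry in section 8 with a short procedure: define a serious adverse event and record such events with the same question in both arms, from randomisation to the last visit. Include subjects who withdraw, where they can be reached.
2. Add that question to the procedures in 7.3, and to 7.6 for those who withdraw, so that the annual report in 11.3 has a defined source.
3. Tabulate serious adverse events by arm. Beside them, report new major depressive episodes by arm from the SCID-I already repeated after the intervention, with the number of subjects assessed.
4. Reconcile section 8 with 11.3 and with the risk statements in the Summary, 10.4 and 10.5.

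The cost is one short form at existing contacts, some effort to reach those who withdraw, and a short protocol amendment.

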### 11.4 End of study report

*<The following text is applicable for studies without an investigational medicinal product.>*

The investigator will notify the accredited METC of the end of the study within a period of 8 weeks. The end of the study is defined as the last patient's last visit.

In case the study is ended prematurely, the investigator will notify the accredited METC, including the reasons for the premature termination.

Within one year after the end of the study, the investigator/sponsor will submit a final study report with the results of the study, including any publications/abstracts of the study, to the accredited METC.

### 11.5 Public disclosure and publication policy

Results of this study will be published in peer-reviewed international scientific journals.

Both positive and negative results will be published. There are no restrictions in the public disclosure of scientific findings resulting from this study.

